### Data collection and management {18a, 18b, 19}

#### Plans for assessment and collection of outcomes

Data collection of outcomes is planned to occur in the participants’ households by trained personnel not involved in the delivery of the program. There will be up to six assessment timepoints per participant depending on the assigned study group (see the “Participant timeline” section). To promote data quality, besides the training of personnel, there will be duplicate measurements for weight and length (or height).

*Study instruments*
The CDE-II, which was developed and validated in Mexico to screen populations for lag and for risk of delay in child development, consists of specific items for fourteen age groups of children aged 1 to 60 months. Assessed developmental areas include gross motor skills, fine motor skills, language, social skills, and cognitive skills. Score results are categorized into three levels: green (normal development), yellow (developmental lag), and red (at risk of development delay) [24].Bayley Scales of Infant and Toddler Development, Third Edition (BSID-III) [33]. This diagnostic test consists of the following scales: (1) cognitive scale, based on the child’s non-verbal responses and measures learning processes, problem solving ability, attention, the ability to count and classify objects, and the ability to play, among other constructs. (2) Language and communication scale, which contains the subscales of receptive and expressive language; the first measures the child’s ability to understand different stimuli, words, or instructions in the environment. The second assesses language development through vocalizations, word use, and sentence construction. (3) Motor scale, which includes the fine motor subscale that measures hand-eye and hand-to-finger coordination and the gross motor subscale that measures the child’s control over his or her body and abilities to move the torso and limbs. (4) Social-emotional scale, which assesses the main milestones of social-emotional development, such as self-regulation, attention, the child’s ability to relate to and interact with family members and strangers, among other temperamental and social aspects. These scales are administered and scored independently, resulting in domain-specific assessments. The cognitive, language, and motor scales are assessed through direct observation of the child’s abilities on various items that are ordered in an ascending order of difficulty. Start (base) and stop (ceiling) criteria determine which test items each child takes. For each item that the child performs correctly, he or she receives a score of 1; if he or she fails to perform the item, the score is 0. The raw score is the sum of correct responses, including items prior to the starting point (base). As mentioned above, the focus of this study is on cognitive, language, and motor development. The socio-emotional scale comprises thirty-five questions of five points each to be answered by the caregiver, so its administration is quick and easy.McCarthy Scales of Children’s Abilities (MSCA). This test is made up of five scales: Verbal, Quantitative, Executive-Perceptual, Memory, and Motor. The combination of the first three scales provides a General Cognitive Index (GCI), which is considered equivalent to the intelligence quotient [34].

We will also collect the following data:
Household socioeconomic and demographic characteristics. Includes information on the composition of the household, state of health, education, employment situation, assets, income, social security, and access to social programs of the members living in the same household as the minor of interest.Characteristics of the mother of the selected child. It explores aspects of community organization, participation in organizations, safety in the neighborhood, family support networks, social-emotional characteristics of the mother (depression, stress, anxiety, and self-esteem), opinion on social roles and distribution of tasks within the home, and the mother’s pregnancy history.Characteristics of children from 0 to 30 months. Includes information on pregnancy, delivery and postpartum of the mother of the selected child, addictions of the mother during pregnancy and breastfeeding of the child, health status, nutrition and education of the selected child, and parenting practices (feeding, hygiene, sleep) of the selected child.Knowledge of physical, neurological, and psycho-affective child development. It explores the appropriation of knowledge of the child’s mother from the information presented in the workshops given by the UKA facilitators.Dissemination and acceptance of the UKA program. Collected information on the knowledge, permanence, and desertion of the program by the families of the selected child.Addictions of the members of the household. Explores the risk factors to which the selected child is exposed due to the consumption of licit and illicit substances by members of the household.The last booklet corresponds to Raven’s progressive matrix test [35], applied to the primary caregiver and nuclear family of the selected child.

#### Plans to promote participant retention and complete follow-up

To promote participant retention, a community commissioner will be identified in each community. These commissioners will be women who support the NPECDP-UKA implementation as translators and interpreters. They will contact the study participants during the intervention, motivating them to attend all workshops and the data collection during the whole duration of the study.

#### Data management

The data management team, based at the National Institute of Public Health, will elaborate capture masks in REDCap for e-tablets [36]. The data capture system will include automated skip patterns and data value range checks according to instrument structure. The data will be securely stored locally in tablets and then transferred to a centralized data management system with a data quality control protocol overseen by the lead data manager. Study staff will employ several strategies to promote data quality, including double data entry, and range checks for data values during study analyses and applying auditable algorithms for the systematization and automatic identification of possible errors in the values of the measured characteristics. Daily visual cross-validation of the data for complex errors, and regular on-site monitoring, the quality and completeness of the data will be reflective of the state of the trial.

#### Confidentiality

To protect participants’ confidentiality, participant data will be labeled using a unique participant identification code that contains no personal identifiers. Access to the collected participants’ data will be restricted to the principal investigator and appropriately trained Institutional Review Board (IRB)-approved research study staff as required. All laboratory samples, completed forms, reports, and other records will be identified using an unlinked unique participant ID number to maintain participant confidentiality.

#### Plans for collection, laboratory evaluation, and storage of biological specimens for genetic or molecular analysis in this trial/future use

In order to know the anemia status of children, hemoglobin will be measured every 3 months. Trained personnel will obtain capillary blood samples for the diagnosis and timely treatment of anemia in children between 6 months and 5 years and pregnant women. For the detection of anemia, the Hemocue Hb 201™ analyzer will be used. This analyzer provides a measurement of total hemoglobin in whole blood, capillary, venous, or arterial, with the same quality as a hematology analyzer. This system is designed for the quantitative determination of hemoglobin at the point of care in primary care areas and is for in vitro diagnostic use only. No storage and future use of this biological material will be needed.

### Statistical methods {20a, 20b, 20c}

#### Statistical methods for primary and secondary outcomes

The effects of the NPECDP-UKA on ECD for primary and secondary outcomes will be assessed by the difference of proportions for binary outcomes and the difference of means for quantitative outcomes. In case there are unbalanced observed characteristics across groups, effects will be estimated with logistic multiple regression for binary outcomes and with multiple linear regression for quantitative outcomes. Covariate-adjusted means or proportions will be obtained after model estimation as predictive margins [37]. Standard errors will be adjusted for clustered data using the method of linearization [33]. Additionally, the difference in difference estimators with propensity score matching will be performed to approximate effects with a quasi-experimental approach [23]. In this analysis, the unexposed group consists of children of caregivers who declined to participate in the NPECDP-UKA but acceded to participate in the evaluation study.

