## Methods

### Design and setting {9}

To assess the effect of NPECDP-UKA on ECD, we will use a cluster randomized stepped-wedge design [20] with an allocation ratio of 1:1. A total of 80 communities will be randomly assigned to four study groups using blocking. Each block will be comprised of four communities (twenty blocks in total) with a similar percentage of indigenous population, social marginality level, and urbanicity measured in the 2010 Census [21, 22]. Within each block, the four treatments will be randomly allocated to communities (each community receiving exactly one treatment).

For ethical reasons, interventions will not be allocated at the individual level. Instead, all study groups consist of communities in which eligible caregivers will be invited to enroll in the NPECDP-UKA, but the program will be deployed sequentially at the community level, according to the timing randomly assigned. This defines the distinctive characteristic between study groups, for example, whereas group A will have a total of 30 months of the exposure to the program at its last assessment; group D, the last study group to be incorporated, will have no exposure to the program during the study and will be measured only once (Table 1). In all study groups, a baseline assessment will be performed before implementing the intervention.

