**Table 1 Tab1:**
[figure not shown]
Study groups, exposure times, and age of children

The main feature of the proposed design is the possibility of comparing groups of children at the same age range but with a different time of exposure to NPECDP-UKA, at the same calendar period. This design feature will allow to eliminate potential confounding cohort effects since children with the same age across study groups will also share the same year of birth. Table 1 shows the age range of children for each study group at different study calendar periods. The upper age limit of the ECD assessment will be 60 months; therefore, the first group of communities to be exposed to the program will include children aged 1–30 months at their first assessment and these children will be aged 31–60 at their final assessment. At given calendar periods (*t* = 2, 4, 6), the group unexposed to the intervention will function as a control group. For example, the last group of communities to be incorporated to the study (group D) will function as a control group at the last calendar period (*t* = 6). This will allow to estimate the effect of NPECDP-UKA on ECD for exposure times of 30 months (group A vs group D), 24 months (group B vs group D), and 12 months (group C vs group D). Given the rapid changes at early ages and considering the first thousand days of life as a critical opportunity window, we consider that the planned exposure times are adequate to detect changes as well as a gradient of the effect with respect to time exposure. Comparisons between groups will be performed cross-sectionally for children of the same age range. There will be a total of six calendar periods, with a time span of 6 months between the mid-point of consecutive periods and an approximate time span of 6 months between consecutive individual measurements.

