#### Relevant concomitant care permitted or prohibited during the trial

There are no restrictions on the involvement of participants who receive other interventions such as government programs. We expect that such exposure will be similarly distributed over study groups under random allocation. In case unbalances in this characteristic are detected, participation in other inventions will be adjusted for in analyses.

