### Sample size {14}

Our main outcome statistic is the proportion of children with developmental lag (yellow category) or at risk of development delay (red category). The effect will be assessed comparing these proportions between the exposed groups and the unexposed group.

Sample sizes were planned so that there are approximately 150 children for each 6-month age interval; this approximates a uniform distribution of observations across age groups and study groups for the relevant age ranges. As mentioned before, given the stepped-wedge design of the study, groups will be incorporated sequentially but comparisons between study groups will be performed at the same study calendar period and for children at the same age interval (see Table 1 for a representation of the stepped-wedge design). Group A will include 1–30-month-old children (*n* = 750); these children will be 31–60 months old at their final measurement and compared to children with the same ages in group D (*n* = 750). This will allow to assess the effect of NPECDP-UKA on ECD after an exposure time of 30 months. Other comparisons are possible. For example, ECD outcomes from group B vs group D (*n* = 900) and group C vs group D (*n* = 1200) at the final study calendar period (Table 1). Table 3 shows the effect size in terms of a difference of proportions given different levels of proportions in the unexposed group (group D), different design effects (DEFF) that consider that measurements in the same community are correlated (DEFF = 1.5, 2.0) [31], a significance level of 0.05 under a bilateral test, and a statistical power of 80.0%.

**Table 3 Tab3:** Sample sizes and effect sizes in terms of a difference of proportions between two groups given a statistical power of 80%

Sample size per group	Proportion in the group without exposure to NPECDP-UKA	Effect size (difference of proportions) given different design effects (DEFF)*		
		DEFF = 1.0	DEFF = 1.5	DEFF = 2.0
750	0.50	0.072	0.088	0.102
900	0.50	0.066	0.081	0.093
1200	0.50	0.057	0.070	0.081
750	0.25	0.065	0.080	0.093
900	0.25	0.059	0.073	0.085
1200	0.25	0.051	0.063	0.073
750	0.125	0.052	0.064	0.075
900	0.125	0.047	0.058	0.068
1200	0.125	0.040	0.050	0.058

*The design effect is a factor that when multiplied by the variance of an estimator under a simple random sampling design corresponds to its variance under a complex sampling design; in this case, a design with clustering of observations within communities

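### The adjustment rules depend on observed imbalance and are not confined to pre-exposure variables, so they can attenuate the primary effect

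*Protocol article*

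**What the plan says.** Under Statistical methods for primary and secondary outcomes, effects "will be assessed by the difference of proportions for binary outcomes and the difference of means for quantitative outcomes". The same paragraph then makes the estimator conditional: "In case there are unbalanced observed characteristics across groups, effects will be estimated with logistic multiple regression for binary outcomes". Quantitative outcomes get linear regression on the same condition. Results are to be reported as predictive margins with standard errors adjusted for clustering.

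The section on concomitant care has a parallel rule for taking part in other programmes: "In case unbalances in this characteristic are detected, participation in other inventions will be adjusted for in analyses". It expects such participation to be similar across groups because allocation is random.

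On timing, Design and setting says that group D "will have no exposure to the program during the study and will be measured only once". The text accompanying Table 1 puts that measurement at t = 6: "group D) will function as a control group at the last calendar period". Design and setting also says: "In all study groups, a baseline assessment will be performed before implementing the intervention". For the longest exposure, Sample size says of group A that "these children will be 31–60 months old at their final measurement and compared to children with the same ages in group D".

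**The concern.** Randomisation protects the comparison for characteristics fixed before the programme starts. It gives no such protection for characteristics measured after one group has been exposed and the other has not. A difference in those may be part of the effect, and conditioning on it moves the estimate from the total effect towards the part that bypasses the adjusted variable.

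Two features of the text open that route. First, the general rule speaks of observed characteristics without saying when they are observed. Second, the rule on other programmes names a post-randomisation covariate outright, so this part is not a detail left for a later covariate list. Some of the other data collected, such as maternal depression and stress or caregiver knowledge, are things that a parenting programme could change. The more a programme changes such a variable, the more likely an imbalance check is to pick it.

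There is also a smaller issue. Under either rule the primary estimator is chosen after seeing the data, so the estimate depends on which imbalances happen to appear.

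**Working it through.** **1. When each contrast is observed (Tables 1 and 2).**

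| Control group | First measured | Comparator already exposed |
|---|---|---|
| B | t2 | A |
| C | t4 | A, B |
| D | t6 | A, B, C |

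The only measurement time that A and D share is t6, after 30 months of exposure in A. The same pattern holds for B at t2 and C at t4, so the point is not special to D.

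**2. Whether each group's own baseline settles it.** A's baseline is at t1, at ages 1–30 months. D's is at t6, at ages 31–60 months. The gap is (6 − 1) × 6 = 30 months, in both calendar time and age. Fixed traits can be compared across that gap. For time-varying traits, an imbalance would mix age and period with any real difference.

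**3. Reproducing the plan's own figure (Table 3).** The effective size per group is n/DEFF, and

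power = Φ{ (d − 1.96·√[2p̄(1−p̄)·DEFF/n]) / √[(p₀(1−p₀) + p₁(1−p₁))·DEFF/n] }.

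With n = 750, DEFF = 1.5 (750/1.5 = 500), p₀ = 0.50, p₁ = 0.412 and p̄ = 0.456, this is (0.088 − 1.96 × 0.03150)/0.03138 = 0.84, so power is 0.80. Solving for 80% power gives 0.0721, 0.0881 and 0.1016 at DEFF 1.0, 1.5 and 2.0. Table 3 states 0.072, 0.088 and 0.102.

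**4. Size if a changed variable enters the model.** Let m be the share of the effect that runs through the adjusted variable. To a first approximation the adjusted estimate is −0.088 × (1 − m): −0.088, −0.066, −0.044 and −0.022 for m = 0, 25, 50 and 75%.

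A simulation checked this with 20 against 20 communities of 38 children (750/20 = 37.5), an unexposed proportion of 0.50, a true difference of −0.088, DEFF of about 1.5 and 400 replicates. One t6 variable was shifted 0.2 SD by the programme. Adjustment was triggered by a cluster-robust p < 0.05 for imbalance, and the estimator was logistic regression with predictive margins.

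| Assumed mediated share | Mean estimate | Power |
|---|---|---|
| 0% | −0.088 | 0.82 |
| 25% | −0.067 | 0.61 |
| 50% | −0.043 | 0.33 |
| 75% | −0.023 | 0.16 |

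The Monte Carlo standard error of a power of 0.61 is √(0.61 × 0.39/400) = 0.024. The trigger fired in about 96–98% of replicates. That is an upper-end figure, because the simulated variable had no clustering of its own. A separate run with full mediation (0.4 SD shift, slightly lower clustering) gave −0.001. With adjustment limited to pre-exposure variables, the estimate stayed at −0.087 to −0.089 and power at about 0.78–0.82.

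The shift, the mediated shares and the significance-test trigger are assumptions. The documents give none of them.

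**The case against.** The strongest reply is that the protocol never says t6 values or variables on the causal path will be covariates. Every group has a pre-exposure assessment, and group D's single measurement is its own baseline. The covariate list, the imbalance criterion and the time of covariate measurement commonly sit in a statistical analysis plan, which is not shown. Methods for additional analyses already treats parenting practices as a mediator in a separate structural equation analysis, so the authors know that this variable is on the path.

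Much of this stands. A reader might infer that the rule selects mediators and adjusts the effect away. The documents do not support that: the text permits such covariates without naming them, and the effect vanishes only under full mediation.

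Some tempting examples are also weak. The item on "parenting practices (feeding, hygiene, sleep) of the selected child" belongs to a module labelled for children aged 0 to 30 months, whereas the A versus D children are 31–60 months old at t6. Water, stoves and food security belong to a community component described separately from the evaluated programme. Referral after a diagnosis applies to every group, and the physical component's referrals are to clinical services. It is therefore plausible, but not shown, that exposure changes participation in other programmes.

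The reply leaves two things untouched. Both passages make the primary analysis conditional on observed imbalance. The concomitant-care passage also commits to a covariate observed after randomisation, and an expectation of balance from random allocation need not hold once groups have had unequal contact: group A is assessed at up to six times and group D once.

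**Conclusion.** The concern holds in a limited form. The two stated rules choose the primary estimator from observed imbalance and do not exclude variables that the programme may have changed. If such a variable is adjusted for, and its path runs in the same direction as the total effect, the estimate moves towards zero roughly in proportion to the mediated share: from −0.088 to −0.067 at 25% and to −0.043 at 50%. If no such variable is selected, or none of the effect runs through it, there is no attenuation. The documents do not allow a choice among these cases, so the figures are a range and not a forecast.

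This does not invalidate the design or the randomised comparison. It is a free improvement: a data-dependent rule can be replaced by a fixed one that keeps the total effect as its target.

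**What to change.** Replace both conditional rules with one prespecified primary model, fitted whatever the observed balance. Include:

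- randomisation block, or the 2010 Census variables used for blocking if twenty block terms are too many for the 40 communities in a two-group contrast;
- CDE-II age group and sex;
- only collected characteristics fixed before exposure, for example the pregnancy and birth history of the index child.

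Keep the predictive margins and the cluster-adjusted standard errors, so the result is still a difference of proportions or means.

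State that the primary effect is not adjusted for participation in other programmes, or for any other characteristic measured after a group's start. Report those descriptively, in a labelled sensitivity analysis, or in the mediation analysis already planned. The model applies equally to contrasts that use B at t2 or C at t4 as control.

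The cost is a few sentences in two sections, with no change to sample size. One check is needed: some pregnancy and birth items sit in the module labelled for children of 0 to 30 months, so confirm that they are available for the older children in group D before listing them as covariates.
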